### Sample Characteristics

We expect to enroll a total of 50 patients in this phase for the pilot trial. We expect that more adult men than women (approximately 60% men vs 40% women) will participate in this study based on the biologically higher incidences of kidney tumors in men. Based on previous research at our institution, we expect our sample to be approximately 25% Hispanic or Latino and approximately 25% Black or African American.

### Data Analysis

Demographics, literacy and numeracy, technology use, and both pre- and postconsultation treatment preferences will be compared between the DA and institutional educational material groups using the Mann-Whitney test for continuous variables. We will also use a Fisher exact test for proportions (R version 4.0.5 [27]) with the mid-p adjustment for a 2 × 2 contingency table (exact2x2 package [28]) and with the ordinary *P* value for an r × 2 contingency table where r>2 [27]. Missing responses will be excluded from the analysis. All statistical tests will be conducted at a 2-sided 5% comparison-wise significance level without adjustments for the number of comparisons.

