### Procedure

Data time points comprise one visit for each participant. The study visit, including the patients’ appointments with their urologists, will last approximately 2 hours. Patients will arrive for their regularly scheduled appointments 50 minutes early. Patients who agree to participate will go through the informed consent process with a member of the study team and will subsequently be randomized to receive the DA or the standard, web-based institutional pamphlet (Figure 1). Prior to their consultation with their urologist, they will answer brief surveys for demographics and literacy or numeracy [18-20]. They will then review the web-based DA or standard institutional material provided by the research team. The study team member will be available only for technical questions while reviewing the materials. Patients will then answer surveys about the material provided, their treatment preferences, and knowledge items (Multimedia Appendix 1) about SKMs’ treatment options.

After reviewing the educational materials and answering the first sets of surveys, patients will attend their appointment with their urologist. Following their consultation, the patients will answer surveys about the visit and the decision-making process and will reindicate their desired treatment at that time.

In the following 3-6 months, a study team member will check patient medical records to assess what management option the patient undertook for the first 3 months after the initial consultation, kidney function at the clinically indicated follow-up visits (typically at least one blood test within 6 months regardless of the treatment), routine blood tests, and reports of tumor stage progression.

The questionnaires administered throughout the study, the web-based DA, and standard institutional website will be administered on electronic tablets while a member of the research team is present to answer technical questions about questionnaire functionality and website navigation problems. We will use the institutional Research Electronic Data Capture system to create and administer surveys [21,22]. An advantage of this software is its ability to create unique links leading to the DA website or the web-based institutional materials, creating a seamless integration of survey responses and DA use and responses. Patients will receive US $50 gift cards as compensation for time spent in review of the study materials.

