### Measures

Prior to reviewing the educational materials, participants will answer questionnaires to collect demographic information (sex, race and ethnicity, and educational attainment), self-described literacy abilities [18], numeracy abilities [19,20], and comfort with using different types of technology. A primary outcome for this pilot study is feasibility of viewing the web DA prior to the appointment, and thus the percentage of patients viewing most or all of the tool will be assessed. Participants will answer questions regarding SKM knowledge after presentation of the educational materials to assess the educational benefit of the DA versus the standard institutional materials. Participants will also indicate their preferred treatment. Just after the patient finishes the urologic consultation, an additional survey will be administered. In this postvisit survey, the questions will include the Decisional Conflict Scale, which consists of 16 prompts with a 5-point Likert scale ranging from 1=“strongly disagree” to 5=“strongly agree” to assess uncertainty in the decision, decision efficacy, and contributors to feelings of uncertainty [23,24]. A second survey assessing the shared decision-making (SDM) process scores will be administered to measure patients’ ability to share during decision-making while considering each treatment’s pros and cons [25]. In the postvisit survey, we ask participants again to indicate their preferred treatment. The measures used for our study analysis are provided in Table 1.

Renal function will also be recorded as an exploratory measure, as well as other major comorbidities represented in the Charlson comorbidity score [26], through a review of medical records for up to 6 months following a participant’s completion of the study.

**Table 1 table1:** Decision-making measures and their corresponding descriptions.

Measure		Description
3-item Subjective Numeracy Scale		Individual numeracy skill based on a summation of self-reported ratings of 3 items, including individual comfort to fractions, percentage, and numerical information, where the rating scale ranges from 1=“not good at all” to 6=“extremely good.”

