## Discussion

### Principal Findings

The study aims to evaluate the feasibility of administering of a web-based DA in the clinic and assessing its effects on decision-making compared with an existing institutional website explaining treatment outcomes of patients with SKMs. We anticipate that the web-based DA will be a feasible intervention to enhance patient knowledge of SKMs, with >80% of participants viewing all of the tool and DA recipients having higher knowledge scores. Early-stage data will be collected on surgical or nonsurgical treatment selection, with the expected outcome of fewer DA recipients choosing surgery as an initial treatment option compared to recipients of the standard institutional material, though the pilot will be underpowered to detect a difference. We will conduct comparative evaluation of the knowledge of patients, decision satisfaction, decisional conflict, and shared decision-making as secondary measures, with expected increases in knowledge, decision satisfaction, and shared decision-making and decreases in decisional conflict among DA recipients.

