### Strengths and Limitations

This study is the first example of a web-based DA for patients with SKMs that incorporates personalized risk-based information to guide treatment decisions. The rigorous approach to evaluating this intervention will pave the way for larger studies that aim to evaluate such web-based tools for patient viewing prior to a discussion with their providers about choosing a management approach. For incidental nodules in particular, accurate understanding of risk associated with the lesion itself (ie, metastasis and cancer-specific death), even if representing cancer, and the risks and benefits of treatment options are key to making decisions that are congruent with the degree of mortality risk. The DA was thus designed to allow patients with SKMs (nearly all incidentally detected) to understand their condition in an interactive, concise manner that facilitates better understanding of their options prior to their discussion with a urologist.

Initial usability testing in phase 2 informed an estimated review time of the given materials in under 30 minutes [17]. Patients who received the DA were more likely to self-report reviewing the DA completely than those who received the standard pamphlet [17], supporting the likelihood of viewing the web version of the tool, indicating that the DA is easily accessible to most populations and is not expected to be burdensome.

There are limitations to our proposed pilot trial, including the relatively small sample size for this initial evaluation of the web-based DA. The pilot RCT will be underpowered for detecting anticipated differences in surgical versus nonsurgical treatment selection with the use of a DA. There are elements of limitations inherent to more pragmatic trial designs, such as the ability of patients to access the tool on the internet with minimal usage direction by clinical staff instead of a highly controlled teaching session, self-report of the amount of content viewed in the DA, and minimal preparatory information or training of patients before using the tool. These elements were allowed for real-world evaluation of such decision support.

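### The unqualified exclusion of missing responses makes no exception for the primary feasibility outcome, where a missing viewing response may itself be a failure

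*Protocol article*

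**What the plan says.** The Data Analysis section describes Mann-Whitney and Fisher tests between the two groups and then states: "Missing responses will be excluded from the analysis". It does not distinguish outcomes, arms or reasons for missingness.

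The Measures section names feasibility as a primary outcome and says that "the percentage of patients viewing most or all of the tool will be assessed". Principal Findings anticipates a feasible intervention, "with >80% of participants viewing all of the tool". Strengths and Limitations lists "self-report of the amount of content viewed in the DA" among the pragmatic features of the design, so the outcome depends on a response that can be absent.

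On timing, the Procedure section says: "Patients will arrive for their regularly scheduled appointments 50 minutes early". Consent, randomisation, the baseline surveys and review of the material all come before the consultation. The order of the last step is also given: "Patients will then answer surveys about the material provided, their treatment preferences, and knowledge items". Strengths and Limitations reports that phase 2 "informed an estimated review time of the given materials in under 30 minutes". According to the Abstract, phase 2 used the printed DA.

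**The concern.** For most outcomes, dropping a missing response loses information. For a feasibility outcome it can do more. The question is whether patients get through the tool before the appointment, so a patient who does not is a failure to be counted. If that patient also leaves the viewing item blank, exclusion takes a failure out of both the count and the denominator, and the rate can only rise.

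The setting makes this plausible. The questions about the material, preferences and knowledge come last in a limited window, so a patient called in early would lose those items first. The review-time estimate comes from the printed version. The section on the intervention says that the web version added graphics and values clarification, and it describes tailoring questions and attribute ratings that belong to the DA.

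Two things are at stake. The first is the feasibility figure, which will inform a larger multisite trial according to the Dissemination Plan. The second is the between-arm comparison of preconsultation preference, if blanks are more common in one arm and are related to what the patient would have chosen.

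**Working it through.** **Inputs.** From the article: 25 patients per arm (Study Setting and Recruitment), anticipated viewing above 80% (Principal Findings), exclusion of missing responses (Data Analysis). Assumed, because the article gives no figure: *m* DA patients without a viewing response, all of them non-viewers, with *m* from 0 to 5. The plan reports no feasibility calculation that could be reproduced.

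**Feasibility.** Let *v* be the number who report sufficient viewing.

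- Missing excluded: *v*/(25 − *m*)
- All randomised to the DA, missing counted as not viewed: *v*/25
- Ratio of the two: 25/(25 − *m*), which is 1.04, 1.09, 1.14 and 1.25 for *m* = 1, 2, 3 and 5

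The excluded rate passes 80% when *m* > 25 − *v*/0.8. For *v* = 20 the right-hand side is 0, so one missing is enough. For *v* = 19 it is 1.25, so two are needed. For *v* = 18 it is 2.5, so three are needed.

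| Viewers | Missing | All 25 as denominator | Missing excluded |
|---|---|---|---|
| 20 | 1 | 20/25 = 80.0% | 20/24 = 83.3% |
| 19 | 2 | 19/25 = 76.0% | 19/23 = 82.6% |
| 18 | 3 | 18/25 = 72.0% | 18/22 = 81.8% |

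Exact 95% intervals are wide in either case: 59.3% to 93.2% for 20/25 and 62.6% to 95.3% for 20/24. The arithmetic is the same whether viewing means all of the tool, as in Principal Findings, or most or all of it, as in Measures.

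**Preconsultation preference.** As an illustration, assume that 12 of 25 patients in each arm truly prefer a nonsurgical option, so the true difference is zero. Assume also that every missing response is in the DA arm and comes from a patient who prefers surgery. Exclusion then gives a spurious difference of 12/(25 − *m*) − 12/25.

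| Missing in DA arm | Spurious difference | Two-sided mid-p |
|---|---|---|
| 1 | 2.0 points | 0.89 |
| 2 | 4.2 points | 0.78 |
| 3 | 6.5 points | 0.67 |
| 5 | 12.0 points | 0.46 |

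This is a deliberately unfavourable one-arm pattern, and none of these differences approaches significance. If missingness is unrelated to arm and preference, exclusion costs precision only.

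**Width of the bounds.** With two missing in each arm, the best-case and worst-case differences lie 2/25 + 2/25 = 16 points apart. That is uncertainty left by the missing values and should not be read as bias produced by the rule.

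**The case against.** The strongest defence is that the exclusion sentence closes a paragraph on between-group tests which does not mention feasibility. Feasibility is a single-arm percentage, described over patients or participants and not over respondents. This is correct, so the inflation is conditional on the rule being applied there. Nothing else in the article says how a DA patient with no viewing response is counted, however, and the only missing-data instruction it gives would remove that patient.

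A reader might infer that the rule necessarily removes patients who run out of time. The documents do not support that. The rule drops missing responses, and a patient who stops early can still report partial viewing and remain in the denominator as a failure. Staff are present while the tablets are used. Fifty minutes less a review of under 30 leaves more than 20 minutes for the other steps, and no statement says that the web version takes longer than the booklet.

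A reader might also infer that the randomised comparison is broken. That goes too far. The timing argument reaches only the preconsultation items directly. The postconsultation preference is asked after the visit, and the management undertaken comes from medical records. The article also states that the pilot is underpowered for treatment selection.

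A similar inference about knowledge scores cannot be put into figures, because the text shown gives neither the number of items nor how blanks are scored.

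Finally, the 80% is an expectation with no decision rule attached, so crossing it does not turn a failed trial into a successful one. That stands, and it limits the consequence.

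**Conclusion.** The concern holds in a conditional form. The plan states an exclusion rule without exception, and for one primary outcome the absence of a response may be the very failure being measured. Applied as written to that outcome, the rule can bias the feasibility rate upward. At 25 patients, one to three silent non-viewers separate a rate of 72% to 80% from one of 82% to 83%. This rests on three assumptions: that the rule is applied to feasibility, that some DA patients leave the viewing item blank, and that those patients did not view enough of the tool. The documents give no missingness rate, so the actual size is unknown and may be zero.

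The preference comparison is a lesser matter. Exclusion can bias it if missingness depends on arm and preference, but the illustrated distortions of 2 to 12 points are small beside the imprecision of a pilot of this size.

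**What to change.** Replace the single sentence with outcome-specific statements:

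- **Feasibility:** the denominator is all patients randomised to the DA, and a patient with no viewing response counts as not viewed. Give the number of such patients beside the rate.
- **Preferences:** report missing responses by arm and add best-case and worst-case bounds on the between-arm difference as a sensitivity analysis. Do not fill a missing preconsultation preference with the postconsultation preference or the charted management. Those are different measurements, taken after the urologist has had an influence.

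The cost is a few sentences and one small table, with no new data. The feasibility figure may come out less favourable. It will also be somewhat too low if a non-responder had in fact viewed the tool: with 20 reported viewers and one unrecorded viewer, the fix gives 20/25 = 80.0% where the true figure is 21/25 = 84.0%. Showing the number missing lets a reader see that range.

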### Ethics Approval

The initial phases of DA development consisting of focus groups, semistructured interviews, and initial usability testing of the printed DA with patients with SKM), as well as the current phase pilot RCT protocol were approved by the New York University Grossman School of Medicine’s Institutional Review Board (s16-010008 and s21-01670).

## Results

The pilot RCT using the web-based DA was funded by the National Cancer Institute on August 10, 2021. After testing the web tool, enrollment will begin on August 29, 2022. We estimate recruitment and data collection to be completed by December 31, 2022, with analysis completed by January 30, 2023.

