**Results:**

This phase will consist of a pilot RCT from August 2022 to January 2023 to establish feasibility and preliminarily evaluate decision outcomes. Previous study phases from 2018 to 2020 supported the feasibility of providing the printed DA in urology clinics before clinical consultation and demonstrated increased patient knowledge about the diagnosis and treatment options and greater likelihood of favoring nonsurgical treatment just before consultation. This study was funded by the National Cancer Institute. Recruitment will begin in August 2022.

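### The estimated end dates for data collection (31 Dec 2022) and analysis (30 Jan 2023) leave no room for the planned 3- to 6-month chart follow-up, so those windows would be cut short

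*Protocol article*

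**What the plan says.** **Timeline.** The Results section says "enrollment will begin on August 29, 2022" and then "We estimate recruitment and data collection to be completed by December 31, 2022, with analysis completed by January 30, 2023". The Results paragraph of the Abstract gives the same span: "This phase will consist of a pilot RCT from August 2022 to January 2023".

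**Follow-up.** Procedure says: "In the following 3-6 months, a study team member will check patient medical records to assess what management option the patient undertook", the period of interest being "for the first 3 months after the initial consultation". The same check covers kidney function at clinically indicated visits ("typically at least one blood test within 6 months regardless of the treatment"), routine blood tests and reports of stage progression. Measures adds that renal function, as an exploratory measure, and Charlson comorbidities are recorded "through a review of medical records for up to 6 months following" the participant's completion of the study.

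The article gives no later date for the end of chart review and mentions no staged or second analysis.

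**The concern.** Recruitment and data collection are estimated to end on the same day, and analysis about a month later. A patient seen near that day would have no chart follow-up when data collection closes, and about one month of it when the analysis is due.

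At stake is the record of what patients actually did. The Abstract states the primary aim as the effect of the decision aid on the choice between surgical and nonsurgical management. Preferences stated before and after the consultation address that choice on the day; only the chart review shows the management that followed. If charts are read too early, an operation that falls after the cutoff but within 3 months of the consultation goes unrecorded, and the patient may be counted as managed without surgery. The article also says that the pilot will inform a larger trial of treatment choice and clinical outcomes, for which these are the most relevant data.

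**Working it through.** **Inputs from the article.** Enrollment opens 29 Aug 2022; recruitment and data collection end 31 Dec 2022; analysis is complete 30 Jan 2023 (Results). Chart windows are 3 months for management undertaken and up to 6 months for the other chart measures (Procedure, Measures). Planned enrollment is 50 (Sample Characteristics).

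**Input assumed.** The article gives no accrual pattern. I assume even accrual from 29 Aug 2022 and vary the last recruitment day from 30 Sep to 31 Dec 2022.

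**Step 1: length of the plan.** From 29 Aug to 31 Dec 2022 is 124 days (about 4.1 months). From 29 Aug 2022 to 30 Jan 2023 is 154 days (about 5.1 months). Both are shorter than 6 months.

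**Step 2: when windows close (window end = enrollment date + 3 or 6 months).**
- First possible patient, 29 Aug 2022: 3 months on 29 Nov 2022; 6 months on 28 Feb 2023.
- Last possible patient, 31 Dec 2022: 3 months on 31 Mar 2023; 6 months on 30 Jun 2023.

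The earliest 6-month date is 29 days after 30 Jan 2023. So 0 of 50 patients can have a full 6-month window at either stated date, whatever the accrual.

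**Step 3: full 3-month windows.** A window is complete at a cutoff if the patient enrolled at least 3 months before it: by 30 Sep 2022 for the 31 Dec cutoff, and by 30 Oct 2022 for the 30 Jan cutoff. Counting days inclusively from 29 Aug, those are 33 and 63 enrollment days. Share complete = qualifying days / recruitment days, capped at 1.

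| Recruitment ends | Recruitment days | Complete at 31 Dec 2022 | Complete at 30 Jan 2023 |
|---|---|---|---|
| 31 Dec | 125 | 33/125 = 26% (about 13 of 50) | 63/125 = 50% (about 25 of 50) |
| 30 Nov | 94 | 33/94 = 35% (about 18) | 63/94 = 67% (about 34) |
| 31 Oct | 64 | 33/64 = 52% (about 26) | 63/64 = 98% (about 49) |
| 30 Sep | 33 | 100% | 100% |

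For every patient to have a full 3-month window by 31 Dec 2022, all 50 would have to be enrolled by 30 Sep 2022, about a month after opening. The article states no such plan.

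**The case against.** The best defence is that data collection here means the study visit. Procedure describes a single visit per participant as the data time point, and Measures places the record review after the participant has completed the study. On that reading 31 December closes the visits, and chart review simply has no date. The dates are also called estimates, and no data lock is set. This reading is possible, but Results does not state it, and Procedure and Measures treat the chart data as part of the study. It also leaves the January 2023 analysis ahead of the follow-up without saying that the analysis excludes it. Nor does condensation into an article explain the problem: the conflict is between dates and durations that are both printed.

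The defence does stand against stronger inferences that a reader might draw:

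- **That most treatment-undertaken data would be missing.** This depends on the accrual pattern. Under even accrual to 31 December, about half the windows are complete at the analysis date; with recruitment ending on 31 October, nearly all are. A treatment given before the cutoff is on record even if the window is still open.
- **That all renal-function data would be missing.** Six months is a ceiling, and blood tests taken earlier count.
- **That patients with open windows would be dropped.** The exclusion rule in Data Analysis concerns missing responses, in a paragraph on demographics, literacy, numeracy, technology use and stated preferences. Treatment undertaken is not named there, so applying the rule to chart data is conjecture.
- **That the primary results are compromised.** Viewing of the tool (the feasibility outcome), stated preferences, knowledge, decisional conflict and shared decision-making are all collected on the visit day and can be analysed by 30 January 2023.

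**Conclusion.** The inconsistency is real and should be fixed; it does not undermine the design. That no patient can have a full 6-month window by either date follows from the stated dates alone. So does the fact that patients enrolled after 30 October 2022 lack a full 3-month window when the analysis is due. The shares of about 26% (31 December) and about 50% (30 January) with a full 3-month window rest on even accrual to 31 December and would be higher if recruitment ended earlier.

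The consequence is truncated follow-up of treatment undertaken, renal function, comorbidity and progression, with late operations unrecorded. The documents do not support a reading in which these data are wholly lost or the visit-day outcomes are affected.

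**What to change.** Either of two changes resolves it:

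1. Separate the end of recruitment from the end of chart follow-up. Close chart review at the last consultation plus 3 months for management undertaken and plus 6 months for renal function and progression, and analyse each after that. If recruitment runs to 31 December 2022, those dates are 31 March and 30 June 2023.
2. Keep January 2023, label that analysis as visit-day outcomes only, and schedule a later analysis of treatment undertaken and the other chart measures.

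In both cases, align the dates in the Abstract and Results with Procedure and Measures.

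**Cost.** A change of wording and dates. Chart review is already planned, so there are no extra visits. The windows close about 2 months (31 March) to 5 months (30 June) after 30 January 2023, so the final report on chart-based measures is delayed by about that much, plus time for the analysis itself. Visit-day results need not wait under the second option.
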